## Objectives {7}

The primary aim of this study is to investigate whether STATAMED reduces the length of hospital stay and 30-day hospital readmission rates (combined primary outcome) in the target population, which comprises adult patients with chronic diseases and/or acute infections (see the “Eligibility criteria {10}”). To achieve this, the following interventions will be implemented: a mandatory case review between the referring physician and the lead STATAMED physician to determine patients’ eligibility for the trial and to collaboratively plan their treatment, standard general medical care delivered in a general medical short-stay hospital ward with approximately 20 beds, discharge planning and follow-up care coordinated by case managers, and post-discharge care delivered by mobile nurses (see the “Intervention description {11a}” for details).

During the case review, diagnoses will be reviewed, and a treatment plan will be agreed upon with the goal of minimising unnecessary diagnostic procedures, avoiding overdiagnosis, and ultimately shortening the hospital stay. Reducing the length of stay is expected to lower the risk of nosocomial complications such as hospital-acquired infections, delirium, immobility, and thromboses, all of which can prolong hospitalisation [28–30].

The 30-day readmission rate will be assessed as part of the primary outcome because it is a widely used and reliable indicator of care quality [31]. The assumption is that if reducing the length of stay through STATAMED compromises the quality of care, this would be reflected in higher readmission rates. However, Damiani et al. [19] found that short-stay wards can reduce length of stay without adversely affecting mortality or readmission rates. Furthermore, follow-up care provided by STATAMED, including support from case managers and mobile nurses, is also expected to reduce readmission rates [21]. By combining these two outcomes—length of hospital stay and 30-day hospital readmission rate—this study aims to evaluate whether a reduction in hospital stay can be achieved without compromising the quality of care for the target population.

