**Fig. 1 Fig1:**
[figure not shown]
Study design

The intervention group consists of all eligible patients (see the “Eligibility criteria {10}”) treated in the STATAMED wards. Eligible individuals must be covered by one of the participating statutory health insurers and meet the eligibility criteria. Claims data will only be provided for individuals insured by one of the participating statutory health insurers.

Additionally, three control groups are planned:Control group 1 consists of patients who meet the eligibility criteria for treatment in a STATAMED ward but receive usual hospital care at a non-STATAMED hospital because their referring entity is located in a cluster assigned to the control phase at the time of treatment. This is the standard control group in the stepped-wedge design, enabling the analysis of each cluster before and after STATAMED is introduced.Control group 2 consists of patients who meet the eligibility criteria for treatment at a STATAMED ward and whose referring entity is located in a cluster assigned to the intervention phase at the time of treatment but who are referred to and receive treatment at a non-STATAMED hospital. This group allows for the examination of possible selection effects (i.e. patients who prefer usual hospital care over STATAMED).Control group 3 consists of patients who meet the eligibility criteria for treatment at a STATAMED ward but whose referring entity is located outside a participating hospital site’s catchment area, resulting in treatment at a non-STATAMED hospital. This group allows for the consideration of additional spatial effects. Figure 2 illustrates the various control groups.

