### Eligibility criteria {10}

#### Inclusion criteria for patients

Patients are eligible for inclusion if they meet the following criteria: They present at a participating referring entity with a general medical condition requiring inpatient treatment as defined by the German Appropriate Evaluation Protocol (G-AEP), have a diagnosis corresponding to an ICD-10 code designated specifically for this project (i.e. conditions relevant to the trial), and are expected to have an uncomplicated course of disease corresponding to a patient clinical complexity level (PCCL) of 0 to 2. Additionally, patients must be at least 18 years of age.

The following list of ICD-10-GM (2023) codes includes exemplary diagnoses relevant to the study but is not exhaustive:I10.01 (benign essential hypertension: with mention of hypertensive urgency)I48.1 (persistent atrial fibrillation)E86 (volume depletion)K59.09 (other and unspecified constipation)I50.14 (left ventricular failure: with symptoms at rest)I20.8 (other forms of angina pectoris)I48.0 (paroxysmal atrial fibrillation) and R55 (syncope and collapse)R07.3 (other chest pain) and K29.6 (other gastritis)N39.0 (urinary tract infection, site not specified)I50.13 (left ventricular failure: with symptoms under mild strain)J20.9 (acute bronchitis, unspecified)J18.9 (pneumonia, unspecified)I50.01 (secondary congestive heart failure)K57.32 (diverticulitis of large intestine without perforation, abscess, or bleeding)E11.91 (type 2 diabetes mellitus: without complications, uncontrolled)R10.3 (pain localised to other parts of lower abdomen)A09.9 (gastroenteritis and colitis of unspecified origin)K29.1 (other acute gastritis)

The complete list of ICD-10 codes can be provided upon request.

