### Intervention description {11a}

STATAMED encompasses a range of interventions designed to ensure continuity of care and improve coordination between hospital and outpatient settings both before and after hospital discharge. The following interventions will be implemented:Short-stay ward: Each participating hospital site will include (or, in the case of very small hospitals, consist of) a dedicated short-stay ward (“STATAMED ward”) for patients with general medical conditions who require inpatient treatment, have a diagnosis matching a STATAMED-specific ICD-10 code, and are expected to have an uncomplicated disease course (see eligibility criteria {10}). The average length of stay in a STATAMED ward is anticipated to be approximately 3 days.Case review: To determine whether a patient is suitable for treatment in a STATAMED ward, a mandatory case review will be conducted between the referring physician and the lead STATAMED physician of the respective STATAMED ward. During this review, diagnoses will be assessed and discussed, eligibility will be confirmed, and a treatment plan will be collaboratively developed. If the lead STATAMED physician approves the admission, a planned admission will be scheduled, specifying the date and time to ensure that the STATAMED ward can prepare for the patient’s arrival and admit him or her without delay.Case manager: Case managers in each STATAMED ward will coordinate interdisciplinary and cross-sectoral treatment planning for the post-discharge period. During the hospital stay, they will participate in medical rounds to support discharge planning. Their responsibilities include assisting patients with urgent social care needs, such as arranging home care services, procuring assistive devices, and securing short-term care home placements. After discharge, case managers will help coordinate necessary therapeutic measures, including organising nursing services, scheduling physiotherapy sessions, arranging home visits by occupational therapists, and making appointments with outpatient physicians. They will also communicate with and involve the patient’s caregivers and relatives as needed. Case managers hold a basic qualification in a medical, therapeutic, nursing, or social care profession (e.g. medical assistants) and have received project-specific training to prepare them for their tasks in the STATAMED trial.Mobile nurses: These nurses will provide follow-up care either at the patient’s home or in a long-term care facility. Their responsibilities include medical tasks such as monitoring vital signs, collecting blood samples for analysis, and performing ultrasounds or electrocardiograms. They also assess patients for functional deficits, provide fall prevention guidance, and report on follow-up care needs. Additionally, mobile nurses can assist with the admission process. If a patient’s regular referring physician is unavailable, the mobile nurse can visit the patient before admission to assess their condition. In such cases, the lead STATAMED physician will be consulted via telemedicine to make the admission decision, and the mandatory referral case review will take place at a later date.

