### Concealment mechanism {16b}

This is not applicable. Patients who meet the eligibility criteria and whose referring entity is located in a cluster assigned to the transition or intervention phase can participate in STATAMED. Before admission to a STATAMED ward, patients must provide informed consent to participate in the project.

The control groups will consist of patients who meet the eligibility criteria but receive treatment at a non-STATAMENT hospital. They will be identified retrospectively based on ICD-10 codes available in the claims data from the participating health insurers.

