### Data collection and management

#### Plans for assessment and collection of outcome {18a}

Claims data from the statutory health insurers participating in the trial (AOK Rheinland-Hamburg and AOK Niedersachsen) will be used as the primary data source. Claims data are secondary data collected by health insurers for billing purposes and are considered reliable and valid. Because they reflect actual treatments provided by physicians and hospitals, they contribute to ensuring external validity. Matching methods will be applied in the analysis to improve comparability between the intervention and control groups, minimising selection bias [44].

To ensure data quality, data will be delivered at two time points by the participating health insurers. The final data delivery is expected at the end of the project period (approximately January 2027). Before this, a preliminary data delivery will take place (approximately June 2026) to check the completeness and plausibility of the data.

Although the outcomes will be measured using claims data, additional data will be collected to ensure the feasibility of the analysis. Table 1 provides an overview of the various data sources.

**Table 1 Tab1:** Data sources

Data set	Description	Utilisation
Claims data from participating statutory health insurers	Secondary data collected by statutory health insurers for billing purposes. The data set includes: patient master data (e.g., sex, year of birth, postal code), outpatient data (e.g., pseudonymised physician number, diagnoses[ICD codes], procedures, billed services), medicines (e.g., ATC code, issuance date, price/amount of reimbursement), inpatient data(e.g., hospital number, diagnoses [ICD-code], procedures, date of inpatient admission and duration of hospital stay, billed case rates)	Measuring primary andsecondary outcomes
Task documentation data	STATAMED-specific tasks performed by the lead STATAMED physician, mobile nurse, and case manager must be documented (e.g., mobile nurses document tasks performed during follow-up care, such as measuring vitalsigns or taking blood samples)	Allows assessment and comparison of implementationacross different STATAMED wards
Information on referring entity	Identification numbers and postal codes of referring entities	Allows assignment of patientlevel claims data to the correct cluster

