### Statistical methods

#### Statistical methods for primary and secondary outcomes {20a}

The two co-primary outcomes (length of hospital stay, 30-day hospital readmission rate) are treated as continuous variables. The secondary outcomes (utilisation of hospital emergency departments, emergency outpatient care, and nonemergency outpatient care, as well as place of discharge) are also continuous except for the place of discharge (home, care facility, other), which is categorial.

Because there are two co-primary outcomes without hierarchical ordering, a correction for multiple testing is required. A Bonferroni correction will be applied, resulting in a one-sided significance level of α/2 = 2.5% for each primary outcome given a global type I error rate of *α* = 5%. However, the Bonferroni method is known to be conservative. As an alternative, the Romano-Wolf procedure [43] may be used, as it more efficiently controls the family-wise error rate by accounting for the dependence structure among outcomes through resampling (see “Sample size {14}”).

When analysing stepped-wedge designs, it is important to account for temporal effects given that each cluster transitions to the intervention in a stepwise fashion. In this study, this is particularly important because the STATAMED wards will gain experience with implementing the intervention over time. Additionally, the longitudinal design of the study necessitates the consideration of calendar time because patient case mix may vary by season (e.g. winter versus summer) due to the focus of the study on general medical conditions. To account for these temporal effects, generalised linear mixed models (GLMMs) and generalised estimating equations (GEEs) will be applied [45–47]. Propensity score matching, considering age, gender, and morbidity, will be used to ensure comparability between the control and intervention groups.

To avoid bias from patients who are transferred to other hospitals during STATAMED treatment or those who meet eligibility criteria but prefer to be treated at a non-STATAMED hospital, the analysis will be conducted according to the intention-to-treat and per-protocol principles [48].

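### The stated matching variables do not name the index diagnosis and leave morbidity undefined, so a difference in diagnosis mix could bias the treated-versus-control comparison of both co-primary outcomes

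*Protocol article*

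**What the plan says.** The section on statistical methods for primary and secondary outcomes {20a} fixes the comparability step in one sentence: "Propensity score matching, considering age, gender, and morbidity, will be used to ensure comparability between the control and intervention groups". The data collection section {18a} gives matching its purpose: "Matching methods will be applied in the analysis to improve comparability between the intervention and control groups, minimising selection bias". Morbidity is not defined in either place.

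Eligibility rests partly on diagnosis. Patients must "have a diagnosis corresponding to an ICD-10 code designated specifically for this project", and they must be patients who "are expected to have an uncomplicated course of disease corresponding to a patient clinical complexity level (PCCL) of 0 to 2". The example codes are varied: constipation, volume depletion, syncope, gastritis, pneumonia, and left ventricular failure with symptoms at rest.

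The two groups are assembled by different routes. On the ward side, the trial design section {8} says: "The intervention group consists of all eligible patients (see the “Eligibility criteria {10}”) treated in the STATAMED wards". Admission follows a suitability check, described under the intervention {11a}: "To determine whether a patient is suitable for treatment in a STATAMED ward, a mandatory case review will be conducted". On the control side, the concealment section {16b} says: "They will be identified retrospectively based on ICD-10 codes available in the claims data from the participating health insurers". The trial design section also requires controls to meet the eligibility criteria.

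Table 1 lists ICD diagnoses among the inpatient claims data, so the index diagnosis is available for both groups.

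**The concern.** A common code list does not produce a common distribution over that list. A referring physician decides which eligible patients to propose, and the lead STATAMED physician decides which to accept. A control needs no such decision, only an eligible stay in the claims data. If the physicians favour, say, dehydration and gastritis over heart failure with symptoms at rest, the ward group will hold more short-stay diagnoses than the controls, and the difference in mean stay will partly reflect who was sent. The same applies to readmission.

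The calendar-time terms in the planned mixed models and estimating equations do not remove this. They absorb changes over time that all groups share, such as the seasonal variation that the section mentions. They do not absorb a difference between referred and non-referred patients in the same period. The step meant to handle that difference is the matching, and age, gender and an undefined morbidity measure need not balance the reason for admission.

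The missing definition carries a second risk. If morbidity is built from diagnoses coded during the index stay, the treatment may affect it, because the case review plans care "with the goal of minimising unnecessary diagnostic procedures, avoiding overdiagnosis, and ultimately shortening the hospital stay". Ward patients could then carry fewer secondary codes than comparable controls for reasons unrelated to their health. This risk is conditional: the protocol does not say that index-stay codes will be used.

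**Working it through.** **The plan's own figures.** The sample size section {14} sets a minimum relevant difference of 15% for both co-primary outcomes and later adopts 20%. These are planning inputs, so there is no derived figure to reproduce. The protocol gives no length of stay or readmission rate by diagnosis and no expected diagnosis mix. The check is therefore a scenario calculation, and every stay, rate and mix below is assumed.

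**Length of stay.** Take two diagnosis groups with mean stays S (short) and L (long), each making up half of the controls, and no treatment effect. The control mean is (S + L)/2. If the share of long-stay diagnoses among ward patients is lower by d after matching, then

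apparent relative reduction = d × (L − S) / [(S + L)/2].

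Example with S = 3, L = 7, d = 0.10: 0.10 × 4 / 5.0 = 8.0%.

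The shift needed to imitate a target effect T is T × [(S + L)/2] / (L − S). For T = 15% in the same example: 0.15 × 5.0 / 4 = 18.8 points.

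| S, L (days) | Control mean | d = 10 points | d = 20 points | Shift for 15% | Shift for 20% |
|---|---|---|---|---|---|
| 4, 6 | 5.0 | 4.0% | 8.0% | 37.5 points | 50.0 points |
| 3, 6 | 4.5 | 6.7% | 13.3% | 22.5 points | 30.0 points |
| 3, 7 | 5.0 | 8.0% | 16.0% | 18.8 points | 25.0 points |
| 3, 9 | 6.0 | 10.0% | 20.0% | 15.0 points | 20.0 points |

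Here d is what remains after matching. If age, gender and morbidity removed half of a raw 20-point difference, the 10-point column would apply.

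**Readmission.** The same formula with assumed 30-day rates in place of stays:

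- 12% against 16% (mean 14%): 0.10 × 4/14 = 2.9% at 10 points, 5.7% at 20 points.
- 10% against 20% (mean 15%): 0.10 × 10/15 = 6.7% at 10 points, 13.3% at 20 points.

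**Direction.** The figures assume a shift towards short-stay diagnoses, which would favour STATAMED. Selecting patients with an expected uncomplicated course makes that direction plausible, but the protocol does not establish it. A shift the other way would hide a benefit by the same amount.

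**Effect of the fix.** If the index-diagnosis group were balanced, d would be zero across groups and this component would vanish, apart from differences within groups.

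**The case against.** The strongest reply is that the point reads too much into one summary sentence. Morbidity is undefined, and Table 1 supplies ICD diagnoses from which it could be built, including the index one. A reader might infer that the plan excludes the index diagnosis. The document does not support that; it supports only that the diagnosis is not named. The full covariate list may also sit in an analysis plan that is not shown. That stands as a limit on how firmly the omission can be put. It does not dispose of the point, because the article does not defer the choice: it names three variables and says that they are to make the groups comparable. Even a morbidity score that used the index code as one input among many would not assure balance on the reason for admission.

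A second reply is that controls are not simply everyone with a listed code. This is right. They must meet the eligibility criteria, which include expected complexity and exclude inpatient surgery and transfers from other hospitals. These criteria narrow both groups, but they do not equalise diagnosis mix within them.

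A third reply is that the protocol plans an intention-to-treat analysis and sets up control group 2 to examine selection. This carries weight. Comparing all eligible patients by cluster phase, wherever treated, would not depend on whom physicians send to the ward. The exposed comparison is mainly the one by treatment received. Some exposure remains because the per-protocol analysis is also planned and the intervention group is itself defined by treatment in the ward.

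A last reply is that the remedy adjusts for a diagnosis that is coded at discharge and can move with work-up. That is a fair caution, and it shapes the fix.

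**Conclusion.** The point holds in limited form. The stated matching set does not name the index diagnosis and leaves morbidity undefined. Ward patients and controls are selected by routes that can produce different diagnosis mixes within a varied code list. No step that the protocol states is sure to remove a same-period difference in mix. The resulting bias falls mainly on the treated-versus-control (per-protocol) comparison.

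For size, a 10-point difference left after matching would give an apparent change in mean stay of about 4% to 10%, against targets of 15% and 20%. This rests on assumed gaps of 2 to 6 days, an even split of diagnoses among controls, and no treatment effect. A reader might infer that diagnosis mix could account for most of the target effect. The documents do not support that: it would take both a wide gap in stay and a large residual shift, and neither can be read from the protocol. With a 2-day gap, 37.5 points would be needed to reach 15%.

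This is a gap worth closing before outcome data are analysed. It does not show that the results will be wrong.

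**What to change.** In the statistical methods section {20a}:

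1. Add a broad index principal-diagnosis group, drawn from the project code list, as a matching variable or outcome-model factor for both co-primary outcomes. Form the groups on clinical grounds and pool rare codes. Purely three-character ICD-10 groups would merge the listed heart failure codes, which differ in severity of symptoms.
2. Define morbidity, and state that it is computed only from claims dated before the index admission.
3. Report a sensitivity analysis without the diagnosis factor, because the index diagnosis is coded at discharge and may itself shift with the work-up. Broad groups limit this but do not remove it.

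The cost is a few sentences in the protocol and analysis plan and some work on grouping codes. No new data are needed, since inpatient ICD codes are already part of the claims data. The researchers are unblinded, so the groups and the look-back period should be fixed before the preliminary data delivery, expected around June 2026.

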### Interim analyses {21b}

No interim analyses are planned.

### Methods for additional analyses (e.g. subgroup analyses) {20b}

To investigate the heterogeneity of treatment effects, various subgroup analyses are planned. These analyses will examine sociodemographic characteristics (age, gender, place of residence) and adherence to the intervention.

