
All patients who receive treatment in a STATAMED ward will receive the full set of trial interventions without further differentiation within the intervention group. However, certain services offered by the case manager or mobile nurse (e.g. follow-up care) may not be medically necessary for some patients, may be declined by some patients, or may not be provided due to capacity constraints. All services provided will be documented, and STATAMED staff will also document any requested services that could not be delivered (e.g. due to capacity constraints).

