### Participant timeline {13}

The participant timeline consists of three phases:Pre-hospital phase: The timeline starts before the hospital stay with an interaction between a potential participant and a referring entity (e.g. a GP), during which the need for hospitalisation is assessed. If the referring entity determines that the potential participant meets the eligibility criteria for the intervention, the STATAMED ward is contacted for the mandatory case review between the referring physician and the lead STATAMED physician. If the eligibility criteria are met, the admission is scheduled to take place approximately 1–2 days later.Hospital phase: Upon provision of informed consent and admission to the STATAMED ward, participants are formally enrolled in the study. The hospital stay is expected to last approximately 3 days on average. During this period, patients receive standard general medical treatment in the STATAMED unit, and case managers assist with interdisciplinary care planning and discharge preparations.Posthospital phase (up to 28 days after discharge): After discharge, follow-up care is available. The mobile nurse may visit the patient at home or in a care facility. Case managers can assist patients during the hospital stay and after discharge, coordinating follow-up care and addressing post-discharge needs.

Figure 3 illustrates the participant timeline, covering the pre-hospital, hospital, and posthospital phases.

All assessments of primary and secondary outcomes will be conducted using claims data from statutory health insurers. Data collection does not require any direct involvement from participants.

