### Methods in analysis to handle protocol nonadherence and any statistical methods to handle missing data {20c}

At the patient level, nonadherence is expected to be minimal because no specific procedures are strictly required of patients once they have decided to participate in STATAMED. Furthermore, claims data are collected by the participating statutory health insurers independently of the progress of the study, making data delivery and quality independent of patient behaviour.

However, nonadherence may occur due to differences in how the various intervention components are implemented in the STATAMED wards. To address this, STATAMED staff members are required to document their tasks, including evidence of the mandatory case review between the referring entity and the lead STATAMED physician before the admission. The mobile nurse and case manager are also required to document their activities. Likewise, STATAMED wards document any request for components of the intervention that could not be carried out (e.g. due to capacity constraints). This information makes it possible to identify and evaluate nonadherence caused by implementation differences at the STATAMED wards.

Nonadherence can also occur at the level of the referring entity, particularly if patients are referred who do not meet the eligibility criteria. Although a mandatory case review is conducted before admission, the lead STATAMED physician cannot verify the accuracy of the information provided by the referring entity until the patient is admitted. If patients are wrongly admitted due to incorrect information provided by the referring entity, these patients will be transferred to a non-STATAMED hospital.

A fundamental challenge in preparing the data is missing information. Because administrative billing data are collected from a wide range of stakeholders (e.g. doctors, pharmacists, hospitals, medical supply stores), inconsistencies and missing data inevitably occur—both from errors early in the documentation process (e.g. incorrectly issued prescriptions) and from problems in later phases of data collection. When handling missing data, each case is reviewed to determine whether imputation is appropriate and, if so, which method should be employed.

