STATAMED comprises a unique combination of interventions, including a general medical short-stay hospital ward and a mandatory case review between the referring entity and the lead STATAMED physician, case managers, and mobile nurses. Analysing the effects of STATAMED thus represents an important contribution to existing research on health services. In addition to the claims data outlined in this protocol, STATAMED wards are required to document the services they provide, allowing for the measurement of the intensity of use. This will enable a more detailed assessment of the effectiveness of the interventions, moving beyond a simple binary measure of whether an intervention was applied or not.

One limitation of this study is that the project timeline does not allow for an investigation of the long-term health consequences of STATAMED for patients. Additionally, claims data will not be available for all patients who participate in the project; only data from those insured by one of the participating statutory health insurers will be available. This limitation could introduce selection bias, as the patient population of the participating health insurers may differ from the general population. However, access to demographic data will allow us to assess the generalisability of the results.

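### Adherence is listed as a treatment-effect subgroup, but it arises mostly after enrolment and only in STATAMED wards, so its strata cannot separate patient need from a difference in effect

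*Protocol article*

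**What the plan says.** The protocol article, section {20b}, gives the purpose first: "To investigate the heterogeneity of treatment effects, various subgroup analyses are planned". It then names the factors: "These analyses will examine sociodemographic characteristics (age, gender, place of residence) and adherence to the intervention". Adherence stands beside three characteristics that exist before treatment, with no distinction drawn.

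Section {11a} explains why services may be absent. Some case-manager and mobile-nurse services "may not be medically necessary for some patients, may be declined by some patients, or may not be provided due to capacity constraints".

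Section {13} fixes the time of enrolment: "Upon provision of informed consent and admission to the STATAMED ward, participants are formally enrolled in the study".

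Section {20c} treats nonadherence differently. For patients it says: "At the patient level, nonadherence is expected to be minimal because no specific procedures are strictly required of patients". It looks mainly to differences in delivery between wards and to wrong referrals, and says of the ward documentation: "This information makes it possible to identify and evaluate nonadherence caused by implementation differences at the STATAMED wards".

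The Discussion describes the service records as "allowing for the measurement of the intensity of use" and expects them to support a finer assessment of effectiveness than a yes/no measure.

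**The concern.** A treatment-effect subgroup needs a variable that is unaffected by treatment and can be identified in both the treated and the control patients. Age, gender and residence meet that condition. Services received do not: they follow from what happens to a patient in and after a STATAMED stay, and no control patient has a value.

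If patients with greater need receive more follow-up and are also readmitted more often, heavy users will look as if they benefit less, or are harmed, and light users as if they benefit more. That pattern would appear even if the effect were the same in everyone. The evaluation is to end in a recommendation on routine care, so a misattributed component effect could colour that advice, although the recommendation concerns the model as a whole.

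**Working it through.** The plan gives no figure for this analysis, so there is none to reproduce. The check sets the sections side by side and then illustrates the possible size.

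**Text**

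1. *Timing.* Enrolment is at consent and admission ({13}). Case managers work during and after the stay, and mobile nurses mainly after discharge ({11a}). The main exception is the case review, which is normally held before admission; {20c} asks for documentation "including evidence of the mandatory case review between the referring entity and the lead STATAMED physician before the admission". So adherence is mostly, not wholly, post-enrolment.
2. *Counterpart.* Controls are identified from claims data of patients treated at non-STATAMED hospitals ({26a}, {16b}). They have no STATAMED service record.
3. *Determinants.* {11a} gives three reasons for non-receipt: no need, refusal, and capacity. The first two are tied to the patient and can plausibly predict readmission.
4. *Adjustment.* {20a} plans propensity matching of intervention to control patients on age, gender and morbidity. It names nothing specific to adherence strata.
5. *Overlap with the outcome.* Follow-up care runs up to 28 days after discharge ({13}), inside the 30-day readmission window ({12}). An early readmission could therefore cut short the services received.

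**Illustration A: no treatment effect.** All inputs are assumed and none is in the protocol. Need is standard normal.

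- logit P(readmission) = -1.5 + 0.6 × need
- logit P(service use) = b × need, with b = 0, 0.5 or 1.0

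Control readmission is 19.8%. Each stratum is set against all controls.

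| b | users | non-users | users vs controls | non-users vs controls |
|---|---|---|---|---|
| 0 | 19.8% | 19.8% | 0% | 0% |
| 0.5 | 22.0% | 17.7% | 22.0/19.8 - 1 = +11% | 17.7/19.8 - 1 = -11% |
| 1.0 | 23.6% | 16.1% | 23.6/19.8 - 1 = +19% | 16.1/19.8 - 1 = -19% |

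**Illustration A with matching.** Suppose each stratum is matched to controls on a morbidity measure that correlates 0.7 with need (again assumed). The spurious contrasts for b = 0.5 to 1.0 shrink to about +5% to +9% in users and -6% to -11% in non-users. Matching removes part of the distortion, not all.

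**Illustration B: the same true effect in everyone.** Risk ratio 0.80, the 20% reduction that {14} calls plausible. Assumed: readmission of 10%, 15% or 20% at average need, odds ratio 1.5 per SD of need, half of patients adherent, each stratum set against all controls.

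| share of variance in receipt due to need | adherent | non-adherent |
|---|---|---|
| 0 | 0.80 | 0.80 |
| 0.5 | 0.94-0.96 | 0.64-0.66 |
| 1 | 1.00-1.02 | 0.57-0.60 |

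With no real heterogeneity, need-driven receipt produces an apparent difference between strata. Receipt unrelated to need produces none.

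**The case against.** The strongest reply is that adherence here need not mean services received by a patient. {20c} expects little patient-level nonadherence and looks mainly to ward implementation and wrong referrals. Table 1 says that task documentation serves to compare implementation across wards. No section classes an unneeded service as nonadherence. On that reading, medical need has little to do with the subgroup. The reply adds that a condensed article leaves definitions and comparators to the analysis plan, and that morbidity matching already addresses need.

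Part of this stands. A reader might infer that adherence is governed by medical need, or that low adherence marks healthier patients. The documents do not support that: need is one of three stated reasons, and patients who decline a service are not necessarily healthier. A reader might also infer that each stratum will be compared with all controls. No section says so; it is a working assumption of the illustrations.

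The rest does not remove the point. {20b} does not restrict adherence to ward delivery, and the Discussion looks to intensity of use for judging effectiveness. The sentence in {20c} on patients rests on nothing being strictly required of them, which does not cover services that were unneeded or declined. Ward delivery was not randomised either, and there are six sites. The objection is to a choice the article makes, namely placing adherence among treatment-effect subgroups, not to detail it omits.

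**Conclusion.** The point holds in limited form. Adherence, understood as services received, is mostly post-enrolment, is observed only in STATAMED wards, and depends partly on need and refusal. Contrasts across its strata mix need, refusal, capacity and any real difference in effect, and cannot be read as heterogeneity in the way that age or gender contrasts can.

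The size is unknown. Under the assumed inputs it runs from zero, through roughly 5-11% with partial matching, to 11-19% in either direction with need-driven receipt and no matching. It is tempting to say that the bias equals the 15-20% effect for which the trial is sized, but that follows from the chosen inputs and not from the protocol. It is equally too strong to say that the analysis would show need instead of effect; it cannot tell the two apart.

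The primary outcomes, the sample size and the main comparison are unaffected. This is a minor point about an additional analysis.

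**What to change.** - Remove adherence from the list of treatment-effect subgroups in {20b}.
- Report patient-level service use, including the intensity of use raised in the Discussion, as descriptive, with separate categories for not needed, declined and not deliverable.
- If delivery is to be studied as an effect modifier, do so at ward level from the undelivered requests that {20c} already has documented. Label it exploratory, because only six sites contribute and ward delivery is not randomised.
- Optionally, add an instrument-based estimate of the effect of receiving STATAMED as a whole, with cluster phase as the instrument. State its exclusion restriction: cluster phase may affect outcomes only through receipt of STATAMED. This answers a different question and does not replace a component analysis.

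The cost is mainly wording. Services provided and undelivered requests are already documented; whether the records tell unneeded from declined services should be checked. The trial gives up patient-level claims about component effects, ward-level precision will be limited, and the optional estimate would have wider intervals.
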